### Randomization

2.6

A total of 28 hospitals were eligible for the trial, comprising 9 Tier-3 Grade-A hospitals, 15 Tier-3 Grade-B hospitals, and 4 Tier-2 Grade-A hospitals, based on China’s tiered hospital classification system. Under this system, hospitals are categorized into three tiers (Tier-1 to Tier-3), with Grade-A representing the highest service quality within each tier. Randomization was performed at the hospital level. All participating institutions were stratified by hospital grades to ensure balanced cluster distribution between the study arms. Hospitals within each stratum were randomly allocated to either the intervention or control group in a 1:1 ratio, using a computer-generated sequence. To maintain allocation concealment, randomization was performed after obtaining each hospital’s consent to participate.

To minimize observer bias, randomization was conducted by a member of research team who was not involved in recruitment or participant enrolment. Due to the interventional nature, masking of researchers and participants was impossible; however, telephone follow-up personnel and trial statisticians remained blind to cluster allocation until the trial was concluded. Regular meetings were conducted among the investigators to monitor research progress and effectively address any issues in this study.

### Interventions

2.7

This multidimensional intervention strategy where pharmacists actively engage across three synergistic domains to optimize antibiotic use. It includes providing structured education and performance feedback to clinicians, implementing evidence-based clinical decision support tools to standardize prescribing, and developing and deploying patient-centered educational materials to facilitate informed decision-making. This intervention aligns with national antibiotic stewardship policies and local health authority regulations, specifically developed to improve appropriate IV antibiotic prescriptions in emergency settings.

#### Training program

2.7.1

Pharmacists conducted monthly educational sessions for ED healthcare providers on the rational use of antimicrobial infusions at the beginning of each month, with actual IV infusion rate feedback provided to the clinical staff every two weeks. The templates of the main training materials adopted by each intervention center are provided in the Supplementary Appendix SA1. The training sessions had been minuted. Final prescription decisions, including antibiotic selection, duration, and route of administration, were determined based on the clinician’s clinical judgment. Physicians were mandated to transfer patients to tertiary care facilities if deemed necessary.

#### Clinical decision support

2.7.2

Evidence-based clinical decision support cards were implemented to optimize antibiotic prescription practices among the clinicians. Physicians conducted comprehensive clinical assessments of patients with CRP levels of > 10 mg/L before initiating antibiotic therapy. Oral antibiotics with high bioavailability are preferred for mild-to-moderate infections, and parenteral administration is limited to cases that meet the following predefined criteria: (1) intolerance to oral medications, including dysphagia and persistent vomiting; (2) clinically significant malabsorption disorders, including severe diarrhea, gastrointestinal disorders, or malabsorption syndromes; (3) lack of suitable oral alternatives; (4) life-threatening infections requiring urgent treatment, such as sepsis and necrotizing pneumonia; (5) poor adherence to oral treatment regimens. Emergency medical staff across all intervention centers utilized a standardized pocket knowledge card, details of which are available in the Supplementary Appendix SA2.

#### Patient education

2.7.3

Structured patient education materials were systematically developed and distributed as part of a comprehensive antimicrobial stewardship initiative to promote awareness of appropriate IV antibiotic use. The educational material, titled “Standardized Intravenous Antibiotic Therapy,” employed health literacy principles to communicate three key messages: (1) indications for appropriate IV antibiotic use; (2) evidence-based recommendations for antimicrobial agents with equivalent efficacy in oral and IV formulations; (3) potential risks associated with unnecessary IV administration. The visually optimized educational materials were distributed by attending physicians during clinical consultations to ensure direct patient engagement at the point of care. The presentation format of the patient education manual is provided in the supplementary materials of this paper (Supplementary Appendix SA3).

Content development followed a rigorous process, including review by infectious disease specialists, clinical pharmacists, and health communication experts, to ensure accuracy and accessibility.

### Follow-up

2.8

This prospective study implemented a two-phase follow-up protocol to optimize data completeness. Trained research staff at each site performed standardized medical record reviews 7- and 14-day post-discharge. All subsequent visits for bacterial URTIs were systematically recorded in an electronic data capture system using standardized case report forms. At the 14-day follow-up, telephone interviews to assess clinical outcomes were conducted by centrally assigned, trained interviewers blinded to participants’ group allocation. Prior to the follow-up period, we developed an online structured questionnaire for telephone surveys, with logic jumps and mandatory fields to minimize manual data entry errors. All interviewers completed a standardized training session before follow-up initiation to ensure consistency in survey administration. This study exclusively used routine clinical data without requiring additional clinical or laboratory tests, minimizing the participant burden and preserving healthcare resources. Patients will be included from August 1, 2025, to January 31, 2026.

### Outcomes

2.9

#### Primary outcome

2.9.1

The primary outcome was the initial antibacterial drug infusion rate in the two study arms, defined as the proportion of eligible patients who received IV antibiotic therapy, assessed from randomization until the end of the intervention (Table 1).

**Table 1 tab1:** Primary and secondary outcomes.

Hierarchy	Trial outcome	Definition	How it was measured
Primary	Infusion rate of antibacterial drugs	Infusion of antibacterial drugs	Hospital records
Secondary	Disease maintenance	Days of respiratory tract infection symptoms keep	Questionnaire by telephone follow-up
Secondary	Adverse drug reaction	Allergic reaction, rash, or pruritus	Questionnaire by telephone follow-up
Secondary	Disease recurrence within 14 days	Patients re-attend the outpatient clinic or the ED of the hospital for treatment	Questionnaire by telephone follow-up
Secondary	Disease recurrence within 14 days	Patients who did not re-attend the outpatient clinic or emergency but re-used the antibiotic infusion after the first visit in the emergency	Questionnaire by telephone follow-up
Secondary	14-day unplanned hospitalization	Patients be hospitalized	Questionnaire by telephone follow-up

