**Methods and analysis:**

This study employed a pragmatic, parallel controlled, cluster-randomized superiority trial design. Outcome assessment and data analysis were conducted in a blinded manner, while treatment administration remained unblinded. A total of 28 hospitals in Zhejiang Province, China, were randomly allocated in a 1:1 ratio. In the intervention arm, a multidimensional intervention embedded in routine emergency treatment will be applied, involving both doctors and patients. The interventions included systematic physician training, clinical decision support cards, and printed educational materials for patients. Patients admitted to the sites assigned to the control arm will receive usual care at the discretion of treating physicians. The primary outcome was the rate of intravenous antibacterial drug infusion during the index admission. Secondary outcomes included the duration of URTI symptoms, adverse events, proportion of eligible patients who received subsequent antibiotics, frequency of re-consultation, and hospitalization within the follow-up period. The final follow-up was completed by 14 days post-discharge. Participants will be included from August 1, 2025, to January 31, 2026.

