#### Eligibility criteria for participants

2.4.2

Eligible patients had to satisfy all of the following criteria: aged ≥ 18 years, had a URTI diagnosis during the baseline and intervention periods, with laboratory tests indicating white blood cells > 10 × 10^9^/L or C-reactive protein (CRP) ≥ 10.0 mg/L, and required the use of antimicrobial agents with at least one focal sign or symptom. Qualifying manifestations included (1) fever, (2) cough, (3) rhinitis (sneezing, nasal congestion, or rhinorrhea), (4) pharyngitis (sore throat), (5) dyspnea, (6) wheezing, or (7) chest pain.

Exclusions would apply to patients with other infections in addition to URTIs; patients who require hospitalization or referral to a higher-level medical institution; individuals unable to tolerate oral medications; special populations, including those with neutropenia, bone marrow suppression, active radio-chemotherapy, immunosuppression, HIV/AIDS, primary immunodeficiency, pregnancy, or severe psychiatric disorders and patients who were not prescribed antimicrobial agents during this visit.

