### Statistical analysis

2.11

This study will adhere to the CONSORT guidelines for cluster-randomized trials. Based on the intention-to-treat principle, a full analysis set (FAS) will be applied to all randomized subjects at all participating hospitals. Per-protocol analysis of the primary endpoint included only participants who underwent interventions. FAS will be used to study baseline characteristics and primary outcome comparison. A two-sided significance level of 5% will be used to determine the statistically significant results.

Pre-specified subgroup analyses for the primary endpoint will be performed as part of the primary analysis. For between-group comparisons, generalized linear models will be used, with treatment group, hospital level as fixed effects and healthcare center as a random effect. Relative risks (RRs)and risk differences with confidence intervals (CIs) will be calculated. Symptom duration will be assessed using Kaplan–Meier curves with 95% CIs. Formal comparisons between the two groups will beperformed using the Cox proportional hazards model, with the treatment group and hospital level as fixed effects and healthcare center as a Gaussian random effect (frailty). A detailed statistical analysis plan will be prepared before data lock.

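### Baseline-period patients are eligible and are not excluded from the primary comparison, so any seen between randomisation and the start of the intervention would dilute the effect; the outcome window is also worded loosely

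*Protocol article*

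**What the plan says.** **Who is counted.** Section 2.4.2 admits adults who "had a URTI diagnosis during the baseline and intervention periods". Section 2.9.1 takes its denominator from eligible patients: "defined as the proportion of eligible patients who received IV antibiotic therapy, assessed from randomization until the end of the intervention". Section 2.11 states that "a full analysis set (FAS) will be applied to all randomized subjects at all participating hospitals". The model given there has treatment group and hospital level as fixed effects and centre as a random effect.

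**When.** Section 2.8 gives a single inclusion window: "Patients will be included from August 1, 2025, to January 31, 2026". It is not divided into baseline and intervention periods. The article dates neither the baseline period, nor randomisation, nor the start of the intervention. Section 2.6 says that "Randomization was performed at the hospital level".

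**Which event.** The abstract says: "The primary outcome was the rate of intravenous antibacterial drug infusion during the index admission". Section 2.9.1 says: "The primary outcome was the initial antibacterial drug infusion rate in the two study arms", and then adds the window running from randomisation to the end of the intervention. Table 1 defines the outcome only as "Infusion of antibacterial drugs", with no visit or window.

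**The concern.** A baseline period normally serves to describe hospitals or to adjust for where they started. Here its patients meet the eligibility criteria, the primary outcome is a proportion of eligible patients, and no later section takes them out. A patient treated in an intervention hospital before the first training session has not been exposed to the programme. If that patient is analysed in the intervention arm, the estimated effect is a mixture of the real effect and zero. The stated model has no period term and no baseline-rate term that could absorb this.

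The wording of the outcome window adds a smaller problem. Three places describe the same outcome in three ways, and none says that each patient contributes one first visit. A patient who returns, or who receives IV treatment only on return, could be handled differently by two analysts who both follow the article.

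At stake are the clarity of the primary estimate and some of the planned power.

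**Working it through.** **1. Reproduce the plan's figure.** Inputs from section 2.5: 14 clusters of 100 per arm, proportions 0.60 and 0.48, ICC 0.04, two-sided 5% unpooled Z-test.

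- Design effect: 1 + (100 − 1) × 0.04 = 4.96
- Effective size per arm: 1,400 / 4.96 = 282.3
- Standard error: √[(0.60 × 0.40 + 0.48 × 0.52) / 282.3] = √(0.4896 / 282.3) = 0.0416
- Power: Φ(0.12 / 0.0416 − 1.96) = Φ(0.92) = 82.2%, against 82% stated
- Dropout: 1,400 / 0.90 = 1,556 per arm, as stated

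The sample-size figures are sound on their own terms.

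**2. Place the patients against the stated window.**

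| Patient seen | Eligible (2.4.2)? | Inside the 2.9.1 window? | Exposed to the programme in intervention hospitals? |
|---|---|---|---|
| Before the hospital is randomised | Yes, if in the baseline period | No | No |
| After randomisation, before the intervention starts | Yes, if that time belongs to the baseline period | Yes | No |
| During the intervention | Yes | Yes | Yes |

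Only the middle row causes harm. Its size depends on dates that the article does not give.

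**3. Size the dilution.** Assumptions, none taken from the documents: a share f of the analysed patients in each arm falls in the middle row; they have no intervention effect; the control rate stays at 0.60; the number analysed stays at 1,400 per arm; the ICC is unchanged. Then the difference is d = 0.12 × (1 − f), the intervention-arm rate is 0.60 − d, and power is Φ(d/SE − 1.96).

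| Share f | Intervention-arm rate | Difference | Power |
|---|---|---|---|
| 0 | 0.480 | 0.120 | 82% |
| 10% | 0.492 | 0.108 | 74% |
| 20% | 0.504 | 0.096 | 64% |
| 30% | 0.516 | 0.084 | 52% |
| 50% | 0.540 | 0.060 | 30% |

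To give the share some scale: the inclusion window is six months, so with even recruitment one month before the intervention started would be 1/6, or about 17%, of patients. The difference would then be 0.12 × 5/6 = 0.10. The 50% row would need three such months and is an extreme case.

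**4. Compare the wordings of the event.** The abstract points to the index contact, and the opening of section 2.9.1 calls the rate initial. Section 2.9.2 defines subsequent antibiotic use so as to leave out the initial prescription, and Table 1 has a separate row for infusion repeated after the first ED visit. All four favour the first visit. Since hospitals were randomised, a window that opens at randomisation cannot be a patient's own observation time. It reads most naturally as the calendar period over which index visits are collected.

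**The case against.** The strongest reply is that the article already keeps baseline patients out. The window opens at randomisation, and baseline rates were evidently known earlier, because section 2.4.1 excludes 15 hospitals on them. The Discussion also says that baseline IV proportion was used as a stratification factor, although section 2.6 names only hospital grade. On that view the baseline period precedes randomisation and the middle row of the table is empty. This may be so, and it is why the point is about possible dilution only. It does not settle the matter: the eligibility text still includes the baseline period, and no date shows that the intervention started when randomisation took place.

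A second reply is that model terms and set definitions can be left to the SAP, which section 2.11 promises before data lock, and that the statisticians are blinded until the trial concludes. That stands. A missing period term is no fault in itself. What needs correcting is an eligibility statement that conflicts with the purpose of the primary comparison.

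A reader might go further and infer that the outcome has two contradictory windows, so that IV given at re-visits counts and early patients are observed for longer. The documents do not support this. The word initial, the abstract, and the separate outcomes for later antibiotic use all point to the first visit, and the randomisation-to-end phrase fits trial-level accrual. A reader might also infer that half of the analysed patients come from the baseline period, or that re-visit IV differs sharply between arms. The documents give no figure for either.

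**Conclusion.** The point holds in a limited form. As written, baseline-period patients are eligible, and those seen after randomisation but before the intervention started would enter the primary comparison and dilute it. The effect on the result is anywhere from nothing, if there are no such patients, to a material loss of power: about 8 percentage points at a 10% share (82% to 74%) and about 18 at a 20% share (82% to 64%). These sizes rest on assumed shares, a constant control rate and no effect before the intervention starts. They are illustrations and not estimates for this trial.

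The event wording is ambiguous rather than contradictory, and the index-visit reading should be confirmed. The reference to randomised subjects is loose in the same way, because patients were not randomised. The sample-size calculation is not affected. This is a clarification to settle before the analysis is unblinded.

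**What to change.** 1. In the abstract, section 2.9.1 and Table 1, use one definition: IV antibacterial given (yes/no) at each patient's first eligible ED visit within the intervention period, with that period's start and end dates stated.
2. In sections 2.4.2 and 2.11, exclude baseline-period patients from the primary FAS. Use them only to compute each hospital's baseline IV rate, and add that rate as a covariate to the stated model.
3. Describe the FAS as the eligible patients of the randomised hospitals.

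This needs changes of wording and one extra cluster-level covariate. With 28 hospitals, an intercept, one treatment term and two terms for the three hospital grades leave 28 − 1 − 1 − 2 = 24 hospital-level degrees of freedom; the covariate takes this to 23. In return it removes possible dilution and should improve precision if the baseline rate predicts the later rate. An added outcome of any IV antibacterial to day 14 is optional, because later antibiotic use is already a secondary outcome.

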### Sample size

2.5

Based on our previous survey, the current antimicrobial infusion rate among patients with URTIs is estimated to be 50%–70%. A sample size of 1,400 participants per group was calculated to achieve 82% power for detecting a difference of 0.12 in group proportions. This was based on sampling 14 clusters of 100 subjects each in control group and 14 clusters of 100 subjects each in the intervention group. The proportion in intervention group is assumed to be 0.48 under the null hypothesis and 0.6 under the alternative hypothesis. The test statistic used is the two-sided Z-Test (unpooled), with an intracluster correlation of 0.04 and a significance level of 0.05. To account for a potential 10% dropout rate, the sample size was increased to 1,556 participants per group.

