#### Secondary outcomes

2.9.2

We estimated the effects of this intervention on several secondary outcomes.

The duration of URTI symptoms was verified by all random patient exit interviews via phone call follow-up after 14 days.Adverse events, severe adverse events, and adverse events related to antibiotics include allergic reactions, rashes, and pruritus.The proportion of eligible patients who received subsequent antibiotics for any reason within 14 days of follow-up was verified by all randomized patient exit interviews via telephone follow-up. Subsequent antibiotic use was defined as any antibiotic use within 14 days of follow-up, excluding initial antibiotic prescriptions.The proportion of eligible patients with URTIs who re-attended outpatient clinics or emergencies within 14 days, and whether antibiotics were prescribed, compared to intervention hospitals and controls.The proportion of eligible patients who were hospitalized within 14 days was verified by all randomized patient exit interviews via phone call follow-up after 14 days, excluding patients referring to the initial ED visit.

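### Table 1 and section 2.9.2 specify different further-antibiotic outcomes, and the Table 1 recurrence rows do not exclude the initial infusion course, so they are linked to the route that the intervention changes

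*Protocol article*

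**What the plan says.** Section 2.9.2 lists as a secondary outcome "The proportion of eligible patients who received subsequent antibiotics for any reason within 14 days of follow-up" and adds: "Subsequent antibiotic use was defined as any antibiotic use within 14 days of follow-up, excluding initial antibiotic prescriptions". Route does not matter, and there is no condition on whether the patient came back. The abstract and section 2.1 also name subsequent antibiotic use as an outcome.

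Table 1 (section 2.9.1) has no row of that name. It has two adjacent rows, both labelled as disease recurrence within 14 days. The first is "Patients re-attend the outpatient clinic or the ED of the hospital for treatment". The second is "Patients who did not re-attend the outpatient clinic or emergency but re-used the antibiotic infusion after the first visit in the emergency". Neither mentions the initial course. By contrast, the hospitalization row is restricted in its label: "14-day unplanned hospitalization".

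For re-attendance, section 2.9.2 has "The proportion of eligible patients with URTIs who re-attended outpatient clinics or emergencies within 14 days, and whether antibiotics were prescribed", with no condition on the reason for the visit or on whether it was planned.

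Table 1 gives the telephone questionnaire as the source for every secondary outcome. Section 2.8 adds record reviews at days 7 and 14: "All subsequent visits for bacterial URTIs were systematically recorded in an electronic data capture system using standardized case report forms".

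**The concern.** The intervention is meant to move patients from infused to oral antibiotics. A secondary outcome that counts only infusions, or that can count completion of the first infusion course, may then differ between arms because the route differs, with no difference in how patients recover. The introduction and conclusion of the article look to a reduction in IV use with clinical outcomes maintained, and re-treatment and re-attendance are part of the evidence a reader would use to judge that.

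Both definitions stand in current text. Unless they are reconciled before data lock, two different numerators can be built from the same patients, and the choice between them could be made after results are known.

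**Working it through.** **1. The definitions applied to the same patients.** No plan figure exists for these outcomes, so the check is to classify typical 14-day histories under each definition.

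| History after the first ED visit | Section 2.9.2 subsequent antibiotics | Table 1 infusion row | Either Table 1 recurrence row |
|---|---|---|---|
| New oral antibiotic, no visit | counts | no | no |
| New antibiotic given at a return visit | counts | no | counts (re-attendance row) |
| New infusion, no clinic or ED re-attendance | counts | counts | counts |
| Initial infusion course continued, no clinic or ED re-attendance | excluded | can count | can count |
| Initial infusion course continued at the clinic or ED | excluded | no | can count (re-attendance row) |

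Neither definition contains the other. The first line is missed by Table 1 altogether. The fourth and fifth lines are excluded by section 2.9.2 but can count in Table 1.

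**2. Treating the two rows as a composite.** The last column shows what a composite repairs and what it does not. It recovers patients re-treated at a return visit. It still loses oral re-treatment without a visit, and it can still count continuation of the initial infusion course as recurrence. Only patients infused at the first visit can continue an infusion course, so that component is tied to route.

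**3. Re-attendance: direction and possible size.** Inputs from the documents: IV rates of 0.60 and 0.48 from section 2.5. That section attaches both rates to one group ("The proportion in intervention group is assumed to be 0.48 under the null hypothesis and 0.6 under the alternative hypothesis"). I take 0.60 as control and 0.48 as intervention, because the aim is a reduction. With these rates the stated power reproduces:

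- design effect = 1 + 99 × 0.04 = 4.96
- effective n = 1,400 / 4.96 = 282.3 per arm
- SE = √[(0.60 × 0.40 + 0.48 × 0.52) / 282.3] = 0.0416
- power = Φ(0.12 / 0.0416 − 1.96) = 82.2%, against 82% stated

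Inputs not in the documents, assumed for illustration: true re-attendance b, equal in both arms; and a share f of infused patients who return to complete the initial course, independently of true re-attendance.

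Observed re-attendance = 1 − (1 − b)(1 − IV rate × f). The spurious difference is therefore (1 − b) × f × 0.12, higher in control.

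With b = 8%:

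| f | Control | Intervention | Difference |
|---|---|---|---|
| 0% | 8.0% | 8.0% | 0 |
| 10% | 13.5% | 12.4% | 1.1 points |
| 20% | 19.0% | 16.8% | 2.2 points |
| 30% | 24.6% | 21.2% | 3.3 points |

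The result depends little on b and strongly on f. At f = 50% the difference is 5.4 points with b = 10% and 5.7 points with b = 5%. The documents give neither the length of an infusion course nor where it is completed, so no value of f can be preferred.

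**The case against.** The strongest reply is that the infusion row is not labelled as subsequent antibiotic use. It sits beside the re-attendance row under the same label, and the two read naturally as non-overlapping parts of one recurrence outcome: those who came back, and those who did not but were infused again. This stands. A reader might infer that Table 1 discards treatment failures who returned, or that it misses most failures. The documents do not support either: returning patients are counted in the row directly above, and no figure shows how failures divide between the rows. The reply does not remove the mismatch, because the section 2.9.2 outcome still has no row and section 2.9.2 describes no such composite.

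A second reply is that nothing in the documents says infusion courses involve return visits, that a recurrence label points to illness rather than continuing treatment, and that coding of visit reason may sit in the case report form or analysis plan. This also stands as to size: the bias cannot be asserted as fact. But the article does write an exclusion of the initial prescription for antibiotic use and a restriction to unplanned events for hospitalization, so the wording for re-attendance is uneven on its face.

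A third point concerns data source. A reader might infer that Table 1 and section 2.8 conflict because visits are also recorded from medical records. They do not: section 2.10 agrees with Table 1 that clinical outcomes come from telephone follow-up. The interviewers are central and blinded, whereas section 2.6 says researchers could not be masked. Making site record review the main source would give up blinded assessment.

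**Conclusion.** The mismatch between Table 1 and section 2.9.2 is real and needs no assumption: they yield different numerators, and following Table 1 loses oral re-treatment without a visit and can count the initial infusion course as recurrence.

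The effect on re-attendance is conditional. If patients return to complete the initial course, such returns would be more frequent in the arm with more IV use and could favour the intervention. The 1.1 to 3.3 points are correct arithmetic on assumed return shares of 10% to 30% and are not an estimate for this trial.

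It would be wrong to infer that the clinical secondary outcomes in general are distorted. Symptom duration, adverse reactions and hospitalization are untouched, as are the primary outcome and its sample size. The change should be made before data lock, but it does not threaten the main result.

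**What to change.** - In Table 1, replace the row limited to infusions in non-re-attenders with the section 2.9.2 definition: any antibiotic, any route, within 14 days, all eligible patients, initial course excluded.
- Label the other row re-attendance instead of disease recurrence, and exclude visits made only to complete the initial course. Use the same wording in section 2.9.2.
- Keep the blinded telephone interview as the source, and use the day-7 and day-14 record reviews as a cross-check.

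The cost is a table edit, matching wording in the analysis plan, and coding of the reason for each return visit. No new data collection round is needed beyond the interview and the record reviews already planned.
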